### Data analysis

#### Qualitative analysis

The semistructured interviews and the FG will be conducted by the research team (JG and JS), audiotaped, verbatim transcribed and analysed following content analysis, using MAXQDA 2022.^86 87^ Qualitative content analysis is a systematic, rule-bound approach orientated towards rules of text analysis laid down in advance and contributes to the intersubjectivity of the analysis procedure regarding the defined interests.^87^ The analytical steps taken by the category system are, first, the summary and the inductive category formation, then second by the explication and the context analysis, finalised by the structuring and the deductive category formation. The category system will then be rechecked by applying it to the material, the research questions and the case itself.^88^ Constant exchange within the study team and the working group for Qualitative Research at the Chair of Social Determinants of Health will ensure the rigour and integrity of the analysis. The analysis will be framed by applying content-analytical quality criteria and reported using the Consolidated criteria for Reporting Qualitative research.^89^

#### Quantitative analysis

Quantitative data analysis will be conducted using the IBM SPSS software (Version 29.0.1.0). During S2, the dataset will undergo a preliminary examination for meaningfulness. This involves checking for the data’s completeness, outliers and plausibility. A descriptive characterisation of the quantitative S2 sample will be performed based on sociodemographic data to gain initial insights into the sample.

For S3, we plan a pre–post design effectiveness evaluation. The baseline data will be compared with the data from t1 to t3. For this, we will conduct multifactorial variance analyses to investigate whether there are differences in the groups of individual intervention time points regarding the primary and secondary outcomes, thus demonstrating the potential effect of the prevention intervention. Additionally, we will perform regression analyses to interpret the relationship between the collected variables, allowing for statements about the influence of individual variables on different outcomes. Similarly, we present a differentiated sample characterisation for S3. In addition, we add a waitlist-controlled component. After collecting data from t0 to t4, we divide participants of S3 into an intervention and waitlist group. We conduct t-tests within each group to analyse the effects between t0 and t1 for the waitlist group and between t1 and t3 for the intervention group. Calculating Cohen’s d helps us quantify effect sizes from these tests. We then use a Z-test to compare Cohen’s d values of both groups to determine if there are significant differences in effect sizes.

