##### Quantitative sample: participants of the intervention (S2, S3)

We aim to survey all participants from the intervention’s piloting (S2) and evaluation (S3) stages. We will use a non-probability sample for recruitment. Participants in the prevention intervention will receive a flyer on recruitment for our study via the German Pension Insurance and the intervention clinics. On the flyer are instructions and online access for our quantitative data collection. In S2, we expect a total of 60 participants. In S3, we intend to include 960 participants for the pre–post design effectiveness assessment. Inclusion criteria are the participation in the prevention intervention and sufficient German language skills. We expect drop-outs, especially during the digital training phase.

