### Quantitative data collection

Quantitative data will be collected from the study participants in S2 and S3 at four different points (t0–t3) through (online) surveys, depicted graphically in figure 3.

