**Figure 3 F3:**
[figure not shown]
Overview of quantitative data collection.

t0 (first survey) transpires when insured persons are confirmed that participation in the prevention intervention is possible.t1 (second survey) takes place at the beginning of the prevention intervention within the first 2 days of the initial inpatient phase.t2 (third survey) is conducted 2 weeks after t1, at the end of the initial inpatient phase.t3 (fourth survey) occurs 12 weeks after the inpatient phase at the end of the 12-week training phase.

The primary outcomes of interest are workability, assessed using the German Work Ability Index^70^; quality of life, using the German WHO Quality of Life-BREF^71 72^; stress levels, evaluated using the Depression Anxiety Stress Scale-21 (DASS-21)^73–75^ and eHealth literacy, which will be assessed using the G-eHEALS^76–78^ and a self-developed instrument for holistic DHL. The secondary outcomes are anxiety and depressive symptoms (DASS-21) and self-efficacy using the SWOP K9.^79–82^ Further information on the validity and reliability of the assessment instruments is provided in ‘online supplemental material 1’. In addition, we are interested in health behaviour as a secondary outcome, which we operationalise as alcohol consumption, smoking, physical activity and dietary behaviour. The training phase behavioural data follow the FITT criteria^83 84^: frequency, intensity, time and type. We will use FITT data to examine participants’ adherence to the eHealth application.^85^ Additionally, sociodemographic data will be collected during survey t1, and behavioural data from the training phase will be gathered during survey t3.

10.1136/bmjopen-2023-081390.supp1Supplementary data

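### The main pre-post analysis appears to take t0, before the wait for admission, as its reference, so waiting-period change is mixed into differences read as the intervention effect

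*Protocol article*

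**What the plan says.** The Quantitative data collection section plans surveys "at four different points (t0–t3) through (online) surveys". The list under Figure 3 gives their timing:

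- **t0:** "t0 (first survey) transpires when insured persons are confirmed that participation in the prevention intervention is possible".
- **t1:** the second survey "takes place at the beginning of the prevention intervention within the first 2 days of the initial inpatient phase".
- **t2:** two weeks after t1, at the end of the inpatient phase.
- **t3:** the fourth survey "occurs 12 weeks after the inpatient phase at the end of the 12-week training phase".

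The Quantitative analysis section then sets out the Stage 3 effectiveness evaluation: "The baseline data will be compared with the data from t1 to t3". Multifactorial variance analyses are to look for differences between time points in the primary and secondary outcomes, "thus demonstrating the potential effect of the prevention intervention".

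The same paragraph adds a waitlist component. It runs within-group t-tests "between t0 and t1 for the waitlist group and between t1 and t3 for the intervention group", converts each to Cohen's d, and compares the two values with a Z-test.

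**The concern.** The article does not say which survey is the baseline. Because t1 is among the points compared with it, and no survey precedes t0, only t0 is left. The interval from t0 to t1 lies before the intervention, apart from up to two days of the inpatient phase. Any change in that interval (regression to the mean, relief or worry after acceptance, spontaneous improvement or decline) enters every comparison that starts at t0.

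This analysis addresses the Stage 3 questions on work ability, quality of life and stress. There is no randomised control group that would expose a change unrelated to the intervention. If time-point differences are read as the plan reads them, a change that happened before admission can be reported as an effect of the programme.

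**Working it through.** **Step 1: which survey is the baseline.** The surveys are t0, t1, t2 and t3. The baseline is compared with t1, t2 and t3. A survey is not compared with itself, so the baseline is t0. This is an inference by elimination; the article never states it.

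**Step 2: what a t0-based difference estimates.** With μ0 to μ3 as the mean outcomes at the four surveys:

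- μ3 − μ0 = (μ1 − μ0) + (μ3 − μ1)
- μ2 − μ0 = (μ1 − μ0) + (μ2 − μ1)

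The first bracket is the waiting-period change and the second is the change during the intervention. The whole waiting change enters the estimate, whatever its sign. The overall time test has the null hypothesis μ0 = μ1 = μ2 = μ3. That is false whenever μ0 ≠ μ1, even if μ1 = μ2 = μ3.

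**Step 3: comparison with the waitlist component.** There, t0 to t1 is the waiting interval and t1 to t3 the intervention interval. The main analysis makes no such division: it neither subtracts t0 to t1 nor uses t1 as the reference.

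**Step 4: illustration of size.** The article gives no power calculation, standard deviation or correlation, so there is no planned figure to reproduce. The only input taken from it is n=960, the Stage 3 target. The assumptions are outcome SD 1, correlation 0.6 between surveys, two-sided alpha 0.05, no change after t1, a paired t0-to-t3 test, and n=500 or n=300 to represent losses.

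SE of the mean change = √(2(1 − 0.6)/n):

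- n=960: √(0.8/960) = 0.0289
- n=500: √(0.8/500) = 0.0400
- n=300: √(0.8/300) = 0.0516

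Probability of significance ≈ Φ(δ/SE − 1.96), where δ is the waiting change in SD units. For δ = 0.10, δ/SE is 3.46, 2.50 and 1.94.

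| Waiting change δ | n=960 | n=500 | n=300 |
|---|---|---|---|
| 0.05 SD | 41% | 24% | 16% |
| 0.10 SD | 93% | 70% | 49% |
| 0.20 SD | at least 97% | at least 97% | at least 97% |

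**Step 5: check by simulation.** There were 1000 runs per setting, with equal correlation of 0.5 or 0.7 among the four surveys and change only between t0 and t1. At δ = 0.10 the rejection rates, from correlation 0.5 to 0.7, were:

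| Test | n=960 | n=480 |
|---|---|---|
| Paired t0 vs t3 | 87% to 98% | 57% to 79% |
| Repeated-measures ANOVA, t0 to t3 | 91% to 99% | 58% to 82% |

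The paired t1-vs-t3 test stayed at about 4% to 6% for every waiting change from 0 to 0.3 SD. That near-nominal rate follows from the assumption of no natural change after t1.

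**The case against.** The strongest reply has four parts.

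- **Baseline is undefined.** The article never equates it with t0, and labels in this section are unreliable: it also mentions a t4 that the survey schedule does not contain. This stands as a caution. If t1 was meant, however, the sentence has t1 compared with itself and needs the same correction.
- **No t0-to-t3 contrast is named as the effect estimate.** The plan is a variance analysis across time points, its wording is hedged, and follow-up contrasts are commonly left to a statistical analysis plan. This stands against treating the paired test above as the planned test; it is an illustration. It does not remove the problem, because the overall time effect across t0 to t3 carries the same mixture and the article says how differences are to be read.
- **The waitlist component handles the wait.** It does separate the intervals, and t0 to t1 will be visible in the data. But it is an addition, and nothing carries its separation into the main analysis.
- **Direction and size are conjecture.** This stands in full. A reader might infer that the bias favours the intervention because people enter while distressed. The article does not establish that: it describes incipient disorders and proactive contact by insurers, and deterioration during the wait would bias the other way.

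A reader might also infer that people who receive the study flyer at a clinic have no t0 and would be dropped. The article says only "Participants in the prevention intervention will receive a flyer on recruitment for our study via the German Pension Insurance and the intervention clinics". It does not say that anyone is first reached at the clinic or after t0.

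**Conclusion.** The point holds as an inconsistency in the main analysis. On the only workable reading, t0 is the reference, and differences from it combine a pre-intervention change with the intervention change. The waitlist component in the same section keeps the two apart. The mixing is an algebraic identity and needs no assumption about direction.

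The amount is unknown. The illustrative figures show only that, at the planned sample size, even a waiting change of 0.10 SD could produce a significant result with no intervention effect. They depend on the assumed correlation, alpha, waiting change and test, and on no change after t1.

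It would go too far to conclude that the effect is biased upwards, or that measuring from t1 gives an unbiased effect. Changing the reference removes only the change before t1. Regression to the mean and natural recovery after t1 remain in an uncontrolled t1-to-t3 change.

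**What to change.** Replace the baseline sentence in the Quantitative analysis section with wording such as: *The pre-intervention reference is t1. Intervention-period change is estimated from t1 to t3 and from t1 to t2. The change from t0 to t1 is reported separately as the waiting-period change. Differences from t0 to t2 or t3, and the overall time effect across t0 to t3, are not interpreted as the effect of the intervention.*

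The report should add that the t1-to-t3 change is uncontrolled and may include natural recovery.

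The cost is a few sentences. No new data are needed, since t1 is already collected. The reported effect may change in either direction.

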**Methods and analysis:**

The study uses a three-stage parallel mixed-methods design. This study accompanies the development (stage 1), piloting (stage 2) and evaluation (stage 3) of the new intervention. Within the stages, there is a quantitative as well as a qualitative research strand. Employed persons with an incipient mental disorder will be included. Additionally, experts within the project or connected areas will be included. Quantitative data will be analysed using multifactorial variance analyses in a pre–post design. Qualitative data will be analysed using qualitative content analysis. The study is a comprehensive research approach to investigate the development, piloting and evaluation of an app-supported psychosocial app-based prevention intervention. The rigour of the study will be achieved through data triangulation.

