#### Stage 3: evaluation (January 2023–April 2026)

Stage 3 (S3) aims to analyse the implementation and execution of the intervention. The key research questions in the evaluation stage are: (1) Is the implementation of the psychosocial prevention intervention achieved? and (2) Is the psychosocial prevention intervention successful?

We will examine organisational conditions, accessibility of the target group and collaboration among the project partners to implement the prevention intervention. We will investigate this from the perspectives of professionals and intervention participants. Additionally, we will assess the effectiveness of the intervention. This results in six qualitative and four quantitative subresearch questions for stage 3.

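### The Stage 3 effectiveness evaluation reads uncontrolled time-point differences as an intervention effect, and the waitlist comparison that could check this is given no role in the conclusion

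*Protocol article*

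**What the plan says.** Stage 3 has two key questions. The second is "Is the psychosocial prevention intervention successful", and the same section says that effectiveness will be assessed.

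The Quantitative analysis section gives two analyses that bear on it.

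- **Pre-post.** "For S3, we plan a pre–post design effectiveness evaluation". The contrast is described as follows: "The baseline data will be compared with the data from t1 to t3". It is carried out by multifactorial variance analyses, and the inference is attached in the same sentence: "differences in the groups of individual intervention time points regarding the primary and secondary outcomes, thus demonstrating the potential effect of the prevention intervention".
- **Waitlist.** "In addition, we add a waitlist-controlled component". Within-group t-tests examine "effects between t0 and t1 for the waitlist group and between t1 and t3 for the intervention group". Each gives a Cohen's d, and a Z-test compares the two.

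The abstract mentions only the first: "Quantitative data will be analysed using multifactorial variance analyses in a pre–post design". The section on the quantitative sample likewise ties the 960 Stage 3 participants to the pre-post assessment. No sentence says what part the waitlist result plays in answering the question of success.

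**The concern.** A difference between time points in a single treated group shows that scores changed. It does not show why. According to the abstract, participants are employed people with an incipient mental disorder. The insurers approach them proactively, and they are surveyed around entry to a programme. In such a group, some improvement from regression to the mean or natural recovery is plausible without any programme.

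The sentence that draws an effect from these differences would count that improvement as an effect of the intervention. If baseline means t0, as a comparison with t1 to t3 suggests, the contrast also includes the wait before any treatment. Moving the baseline to t1 would not cure this, because the comparison would still be uncontrolled.

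At stake is the answer to the second key question of Stage 3. With several hundred participants, a small background change is enough for a significant result. The waitlist contrast asks the more relevant question, whether scores changed more during the programme than during waiting, and uses surveys that are collected anyway. As written, its result need not affect the conclusion.

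**Working it through.** **Inputs from the article.** 960 participants in Stage 3 and 60 in Stage 2. t0 is at confirmation of participation, t1 at the start of the inpatient phase, t2 two weeks after t1, and t3 twelve weeks after the inpatient phase. So t1 to t3 is about 2 + 12 = 14 weeks. The length of t0 to t1 is not given.

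**Reproducing a stated figure.** 60 + 960 = 1020, which matches the expected total. The article contains no sample-size calculation to reproduce.

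**Assumptions (none are in the article).** True intervention effect zero; two-sided 5% level; background improvement (drift) of 0.05 or 0.10 SD per interval; within-person correlation r of 0.4, 0.6 or 0.8; 960 or 300 participants analysed, since drop-out is expected but no rate is given; an equal split for the waitlist comparison.

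**Step 1: pre-post test, t1 to t3.** The standardised change is dz = drift / √(2(1 − r)), and the probability of significance is Φ(dz√n − 1.96) + Φ(−dz√n − 1.96).

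For drift 0.10, r = 0.6, n = 960: dz = 0.10 / √0.8 = 0.112; dz√n = 3.46; Φ(3.46 − 1.96) = 0.93.

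| n | Drift (SD) | r = 0.4 | r = 0.6 | r = 0.8 |
|---|---|---|---|---|
| 960 | 0.10 | 81% | 93% | 100% |
| 960 | 0.05 | 29% | 41% | 69% |
| 300 | 0.10 | 35% | 49% | 78% |
| 300 | 0.05 | 12% | 16% | 28% |

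With 960 participants, an observed standardised change of 1.96 / √960 = 0.063 is already significant.

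**Step 2: waitlist contrast with equal drift in both intervals.** With m = 480 per half, the standard error of the difference in d is √(1/m + d₁²/2m + 1/m + d₂²/2m). For d₁ = d₂ = 0.112 this is 0.065. The expected difference is zero, so the Z-test favours the programme in about 2.5% of trials.

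**Step 3: waitlist contrast when the wait is shorter.** Suppose drift is linear in time and t0 to t1 is a quarter as long as t1 to t3. The waiting-period d is then 0.112 / 4 = 0.028. The difference is 0.084, and 0.084 / 0.065 ≈ 1.30. The chance of a falsely favourable result is Φ(1.30 − 1.96) ≈ 25%. With a wait half as long, the difference is 0.056, the ratio is 0.86, and the chance is about 14%.

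**Step 4: precision.** The single-group change in 960 people has a standard error of about √(1/960) = 0.032. The contrast between halves has 0.065, which is twice as large.

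**The case against.** The strongest reply is that ranking analyses is commonly left to the full plan, which is not shown, and that two analyses joined by an addition do not contradict each other. That stands: the missing hierarchy is not counted here as an error. What remains is an inference that the article does state, namely that differences between time points demonstrate a potential effect.

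A reader might go further and infer two rival analyses of equal standing, with the sponsor free to pick the favourable one after seeing both. The article does not support this. The abstract, the sample-size sentence and the analysis section all lean towards pre-post. Both analyses are written down in advance, and the ethics section commits to transparent reporting. The problem is that the favoured analysis cannot carry the conclusion attached to it.

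The Stage 3 sub-questions ask what effect the intervention has, without a pass/fail rule, and the sentence is hedged by the word potential. Both points are fair, and they argue for a wording change rather than a redesign. Still, attributing change to the intervention needs a comparison even when the aim is estimation.

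The direction and size of drift are assumed. The introduction describes work stress becoming chronic, so scores could worsen without treatment and pre-post could understate benefit. No document says that people were selected on high scores on the outcome scales. This limits the percentages, but in either direction the pre-post difference mixes drift with effect.

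Finally, the waitlist contrast has weaknesses of its own. The waiting interval has no stated length. The groups are divided after data collection by a rule the article does not give. The text also refers to a t4 that is not among the four surveys described. A reader might therefore want it to decide the question alone; Step 3 shows why that would be unsafe.

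**Conclusion.** The point holds in this form: the planned effectiveness evaluation attaches an effect inference to an uncontrolled comparison, while the partly controlled comparison has no stated role in the conclusion. This is more than missing detail, because following the text as written can turn background change into a claimed effect.

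With no intervention effect, the pre-post test is significant in about 93% of trials at a drift of 0.10 SD, r = 0.6 and 960 participants. Over all settings examined, the figure runs from 12% to nearly 100%. These are illustrations under assumed drift, correlation and significance level, not predictions for this study. The waitlist contrast holds at about 2.5% in favour of the programme only if drift is the same in both intervals. It rises to about 25% with a quarter-length wait and linear drift. It is therefore a necessary support for an effect claim, not a sufficient one. The article should be changed on this point, mainly in its wording.

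**What to change.** In the Quantitative analysis section:

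1. Delete the clause that reads time-point differences as demonstrating a potential effect.
2. Label the pre-post variance analyses as descriptive of the course over time.
3. State that any claim of an intervention effect, in answer to the second Stage 3 question, must be supported by the contrast between intervention-period and waiting-period change.
4. Record each participant's t0 to t1 interval, and report the contrast with a sensitivity analysis that scales change to interval length.
5. Fix the division into intervention and waitlist groups by a rule that does not depend on outcomes.
6. State the limits that remain, including that the two intervals may not be comparable.

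Bring the abstract into line so that it mentions the waitlist comparison.

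**Cost.** No new outcome surveys are needed; the additions are the interval dates and one sensitivity analysis. The real price is precision. With two equal halves the standard error of the contrast is about 0.065 against 0.032 for the single-group change, so an effect claim becomes clearly harder to reach.

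### Variance analyses over time-point groups and within-group t-tests suit repeated surveys with expected drop-out poorly: standard errors or the t3 effect may be wrong, in a direction the plan does not determine

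*Protocol article*

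**What the plan says.** Under Quantitative data collection, the protocol article defines four surveys of the same participants. t0 comes when participation is confirmed, t1 at the start of the inpatient phase, t2 at its end, and t3 at the end of the 12-week training phase.

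Under Quantitative analysis, the S3 evaluation is described as pre–post: "The baseline data will be compared with the data from t1 to t3". The method is multifactorial variance analysis, used to look for "differences in the groups of individual intervention time points regarding the primary and secondary outcomes". A waitlist component follows: "We conduct t-tests within each group to analyse the effects between t0 and t1 for the waitlist group". Those assigned to the intervention arm are tested over t1 to t3 instead. Finally: "We then use a Z-test to compare Cohen’s d values of both groups".

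Under Quantitative sample: participants of the intervention (S2, S3), the article states the S3 size, "In S3, we intend to include 960 participants", and adds: "We expect drop-outs, especially during the digital training phase". It gives no rate and no reason for leaving.

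**The concern.** Time points are repeated measurements on the same people, not groups of people. The named variance analysis can be run in two ways, and each has a cost.

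- **Time as a between-subject factor.** The within-person correlation is ignored and the standard error of change is wrong.
- **Classical repeated-measures ANOVA or paired t-tests.** These use only people with all the surveys concerned. Anyone without t3 is lost from the t1–t3 comparison, although their t1 and t2 scores have been collected.

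The research questions ask about the effect in participants, not only in those who finish the app phase. If leaving is related to progress, people with complete data are a selected subset, and a larger sample does not remove that.

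The Z-test is exposed as well. Its t0–t1 side ends before the digital phase and its t1–t3 side spans it, so the expected loss falls mainly on one side of the plan's only controlled comparison.

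**Working it through.** **The plan's own figure.** S2 plus S3 is 60 + 960 = 1020, which matches the total expected to undergo the intervention. The article states no power, SD, correlation or drop-out rate, so there is nothing further to reproduce. Correlations and drop-out rates below are assumptions.

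**Step 1: ignoring the pairing.** For scores with SD 1 and within-person correlation r, the standard error of a mean change is √(2/n) if the time points are treated as independent, and √(2(1−r)/n) if they are paired. The ratio is 1/√(1−r). With n = 960:

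- unpaired: √(2/960) = 0.046
- paired, r = 0.5: √(1/960) = 0.032, ratio 1.41
- paired, r = 0.7: √(0.6/960) = 0.025, ratio 1.83

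The mean change itself is not shifted by ignoring the pairing. With complete data the error is conservative.

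**Step 2: how many are lost.** If 20% to 40% of the 960 lack t3, a t1–t3 pair is missing for 192 to 384 people.

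**Step 3: which way the bias goes.** With equal correlation r between all surveys and SD 1:

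- covariance of the t1–t3 change with the t1–t2 change: r − r − r + 1 = 1 − r, positive. If those with little early gain leave, complete pairs overstate.
- covariance with the t1 score: r − 1, negative. If those worst at t1 leave, complete pairs understate.
- covariance with the t2 score: r − r = 0. If those worst at t2 leave, complete pairs are unbiased.

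**Step 4: size.** Simulation with n = 960, four surveys, true t1–t3 change 0.40 SD (higher is better), logistic drop-out slope 1 per SD and 60 runs per setting. Results for r = 0.5 and 40% missing at t3:

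| Who is missing at t3 | Unpaired, available cases | Complete pairs | Mixed model |
|---|---|---|---|
| Random | 0.40 | 0.40 | 0.40 |
| Worse at t2 | 0.57 | 0.40 | 0.41 |
| Better at t2 | 0.23 | 0.39 | 0.40 |
| Little t1–t2 gain | 0.39 | 0.55 | 0.39 |
| Large t1–t2 gain | 0.40 | 0.24 | 0.40 |
| Worse at t1 | 0.56 | 0.23 | 0.40 |
| Worse at t3 (unobserved) | 0.74 | 0.58 | 0.63 |
| Better at t3 (unobserved) | 0.07 | 0.23 | 0.18 |
| Little t1–t3 gain (unobserved) | 0.56 | 0.73 | 0.62 |

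Across r = 0.5 and 0.7 and 20% and 40% missing, with drop-out depending on observed scores (MAR), the unpaired estimate ran from 0.16 to 0.64 and complete pairs from 0.23 to 0.55. The mixed model stayed at 0.39 to 0.41. With drop-out depending on unobserved t3 scores (MNAR), the mixed model ran from 0.18 to 0.63.

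**The case against.** **The wording may only be loose.** The abstract places the variance analyses in a pre–post design, and t-tests within a group between two time points are most naturally paired, although the article does not use that word. The between-subject reading is therefore the less likely one. A condensed article may also leave missing-data handling to a fuller document. Both points are fair, and the absence of missing-data detail is not the criticism. What remains is that the methods the article names, on their natural reading, use complete cases or pairs, and the article itself expects loss just before the last survey.

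**A reader might infer that the t3 effect is overstated,** because people who benefit least leave. The documents do not support that. They say only that drop-out is expected and when. Step 3 shows upward, downward or no bias, depending on who leaves. Ignoring the pairing is no route to overstatement either, since by itself it affects only the standard error.

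**A reader might also infer that a mixed model cures the problem.** Its good performance under MAR is largely built in, because drop-out there depends on scores the model uses. Under MNAR it was further from the truth than complete pairs in two of three scenarios (0.63 against 0.58, and 0.18 against 0.23) and closer in the third (0.62 against 0.73). Nor does it turn an uncontrolled pre–post comparison into a controlled one.

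**Some data may not exist.** Under Ethics and dissemination, withdrawal of consent generally leads to deletion of the person's data. No model recovers those scores.

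**Conclusion.** The point holds in limited form. The named analyses either ignore within-person correlation, with standard errors of change about 1.4 to 1.8 times too large at r = 0.5 to 0.7, or discard people without t3 whose earlier scores are available. In the second case the t1–t3 effect, and so its comparison with t0–t1, may be biased. In the MAR simulations the error of complete pairs reached about 0.15 to 0.17 SD either way on a true change of 0.40 SD (0.55 − 0.40 and 0.40 − 0.23). Those sizes rest on assumed correlations, drop-out rates and selection strength. Neither the direction nor the presence of bias can be settled from the article, and with purely random drop-out there is none. The change is worth making because the alternative agrees with the complete-pair result when drop-out is random and removes the bias when observed scores explain it.

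**What to change.** Replace the variance analyses and t-tests by one linear mixed model per outcome (SPSS MIXED, in the software already named). Use categorical time, an unstructured within-person covariance, and all available t0–t3 scores from everyone with at least one survey. Take the t0–t1, t1–t2 and t1–t3 contrasts from the model. The t0–t1 contrast must stay, because it carries the waitlist-period comparison. If participants are still divided into two groups, add group and group-by-time terms.

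The model assumes that missingness is explained by observed scores. Add MNAR sensitivity analyses, for example one setting t3 non-responders to no change from t1 and one delta-adjusted analysis over a stated range. Report how many participants' data were deleted after withdrawal of consent, since they lie outside any of these analyses.

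The cost is a change of analysis wording and the extra sensitivity runs. No new data or software is needed.
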